### Description and diagram of trial design

The town of Uvira was divided into sixteen clusters stratified into two groups due to the project funding structure and planned works sequence: South (*n* = 6, areas primarily served by the existing tank) and North (*n* = 10, areas primarily served by the new tank) (Fig. 1). The existing and new tank will both eventually belong to the same water supply network and contribute to improving water service across all clusters. The primary criteria used to define clusters were the total length of pipes to be rehabilitated or installed and the number of new community taps; the secondary criteria included considerations such as alignment with existing administrative zones and natural features such as rivers. Key characteristics of the study clusters are presented in Table 1.

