### Analysis plan

The SW-CRT and ITS analyses are detailed hereafter.

A generalised estimating equations (GEE) Poisson regression for rates will be used with robust standard errors. An indicator of water service quality will be included, which may integrate users’ distance to taps, hours of water availability, or volumes distributed, for example, to reflect improvements brought by the intervention in terms of water service. To account for seasonality a harmonic term for time (in months) will be included. This analysis accounts for correlations between individuals within clusters, as well as repeated measures of the same clusters over time. A small sample correction will be considered to adjust for the small number of clusters [57]. Note that data collected during the transition period for each cluster will not contribute to the analysis.

Since the intervention takes place over less than 2 years, the seasonal pattern of cholera infection may not be estimated correctly using only data from the trial period. A sensitivity analysis will be carried out using historical data from the cholera treatment centre which is available from 2009 to the start of the trial. The model will be re-fitted using the same covariates, with all historical data considered non-intervention time. We will also consider the inclusion of a treatment by time interaction term in the GEE model as part of further sensitivity analyses linked to seasonality.

An intention-to-treat analysis will be carried out for the main analysis. The above models will be repeated with the other primary outcome: rate of confirmed cholera cases per 1000 residents.

Randomisation may be particularly challenging to ensure given the nature of the intervention. If the randomisation scheme is not adhered to, balance between arms cannot be assumed. In this case, relevant confounders which may be associated with intervention allocation and outcome will be included in the main analysis, as they would be in non-randomised settings. These may include patient’s age and sex, and factors related to their household location such as water service quality and distance from the cholera treatment centre.

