### Sample size

The “steppedwedge” command was used within Stata 16 (StataCorp LLC, College Station, TX, USA) to calculate the minimum detectable difference (MDD) in the main SW-CRT analysis given known parameters. The pre-intervention cholera rate across all clusters was assumed to be 0.4 per 1000 people per month (Table 1). Power was set at 80% with a 5% significance level. The calculation was carried out with the intraclass correlation coefficient (ICC) set at 0.3 and mean cluster size 16,000. ICC, average cluster size and cholera rates were found using the historical data (Table 1). The MDD was 0.1 per 1000, corresponding to a decrease to 0.3 per 1000 people (or increase to 0.5 per 1000) or a 25% reduction in suspected cholera incidence. In a meta-analysis, availability of piped water on premises compared to unimproved water sources was found to reduce the risk of diarrhoeal disease in children by 23% (confidence interval 7–36%) [34].

A sample size calculation for the ITS analysis was also carried out. Follow-up periods of 6 and 12 months from an end date of July 2022 were considered. Mean cholera rates per month were estimated using historical data from the CTC in a quasi-Poisson model with a linear term for year and harmonic terms for month. These were used along with estimates of variance and over dispersion parameters to find the minimum detectable difference. The mean monthly rate per 1000 people was estimated to be 0.25 over a 12 month follow-up, 0.29 over 6 months. The minimum detectable reduction in cholera rates was therefore estimated to be 65% with a follow-up time of 12 months, and 75% for 6 months.

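### The primary GEE adjusts for calendar time only through a seasonal harmonic, so non-seasonal city-wide change that runs with the roll-out is read as intervention effect

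*Protocol article*

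**What the plan says.** The Analysis plan section of the protocol article sets the main model: "A generalised estimating equations (GEE) Poisson regression for rates will be used with robust standard errors". For calendar time it says: "To account for seasonality a harmonic term for time (in months) will be included". An indicator of water service quality is also included, to represent what the intervention changed. The same model is repeated for confirmed cases, and transition-period data are dropped.

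The section sees a weakness in the seasonal term: "Since the intervention takes place over less than 2 years, the seasonal pattern of cholera infection may not be estimated correctly". Its answer is a sensitivity analysis that adds the treatment centre's data from 2009 onward: "The model will be re-fitted using the same covariates, with all historical data considered non-intervention time". A second sensitivity analysis is tentative: "We will also consider the inclusion of a treatment by time interaction term in the GEE model". So is the allowance for few clusters: "A small sample correction will be considered to adjust for the small number of clusters".

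The Sample size section handles time differently for the interrupted time series (ITS). There the historical rates were modelled "in a quasi-Poisson model with a linear term for year and harmonic terms for month", and the projected rates are 0.25 per 1000 per month over 12 months of follow-up and 0.29 over 6 months. The stepped-wedge calculation assumes 0.4.

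**The concern.** In a stepped wedge, the exposed share of the population grows as the calendar advances. Randomising the order protects against secular change only if clusters are compared within the same calendar period, which requires a period effect or an adequate smooth function of time. A 12-month harmonic is periodic and cannot represent a decline over years, an outbreak or a one-off drop. What it leaves over is partly aligned with exposure and moves the effect estimate.

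There is also a variance problem. The sandwich estimator treats the 16 areas as independent. An outbreak month that hits all of them together breaks that assumption, and the harmonic does not remove it.

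The article gives reasons to expect such change. Its ITS model carries a year term. The Discussion names vaccination and COVID-19 control as threats to attribution, and says the new tank, which serves all clusters, comes into use half-way through the cluster works. At stake is whether the primary result is a randomised comparison or a seasonally smoothed before-after one.

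**Working it through.** **1. The plan's own detectable difference.** Inputs from the Sample size section: rate p = 0.4 per 1000, cluster size m = 16,000, ICC 0.3, 80% power, 5% significance (two-sided assumed). I used the Hussey-Hughes variance with a random cluster intercept, splitting p(1−p) by the ICC and taking m per cluster-period. MDD = (1.960 + 0.842) × SE.

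| Set-up | Period effects | No time effects |
|---|---|---|
| 16 steps of 1 cluster | 0.078 | 0.054 |
| 16 steps, 2-period transition | 0.089 | – |
| 8 steps of 2 clusters | 0.109 | 0.072 |

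All of these round to the stated 0.1 per 1000. The number of steps entered is not given, so the printed figure does not show which time structure was assumed.

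**2. How large a trend the article implies.** Table 1 sums to 105.6 cases per month in 260,962 people, or 0.405 per 1000. Two slopes follow from the stated figures, taken over 9.4 years:

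- From Table 1: ln(0.25/0.405)/9.4 = −0.051, about −5% per year.
- From the Study setting section, 3.4 per 1000 per year (3.4/12 = 0.283 per month): ln(0.25/0.283)/9.4 = −0.013, about −1.3% per year.

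The baselines do not agree. Table 1 divides 2009–2018 cases by the March 2018 population. The section's own 1266 admissions over 280,000 people give 4.5 per 1000 per year, not 3.4. The slope is therefore uncertain.

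**3. Null rate ratio under a smooth trend.** I fitted Poisson models to expected counts from Table 1 populations, rates and sequence, with no intervention effect, cluster intercepts, a harmonic, and a two-month transition removed.

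| Analysis | −5% per year | −1.3% per year |
|---|---|---|
| Trial period (1 or 12 months before, 0 or 12 after) | 0.91–0.96 | 0.98–0.99 |
| Historical re-fit | 0.71–0.75 | 0.92–0.93 |

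Hand check of the re-fit: the midpoint of the 111 months of history lies roughly 6 years before the average exposed month. exp(−0.051 × 6) = 0.74 and exp(−0.013 × 6) = 0.92.

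**4. Shared irregular shocks.** I ran null simulations, 400 per scenario, using Table 1 populations and cases. Order was randomised within strata, South first, with 3 months before and after. The model was an exchangeable Poisson GEE. Assumptions not in the article: city-wide AR(1) shocks with autocorrelation 0.6, cluster-month overdispersion SD 0.4 on the log scale, seasonal amplitude 0.4. Harmonic-only results:

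| Shock SD | Empirical SD of log RR | Mean robust SE | Ratio | False positives |
|---|---|---|---|---|
| 0.2 | 0.171 | 0.080 | 2.1 | 37% |
| 0.4 | 0.323 | 0.091 | 3.5 | 56% |
| 0.6 | 0.452 | 0.105 | 4.3 | 67% |

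A second set of null runs on Table 1 gave 24%, 47% and 62%, with standard errors about 1.7 to 3.6 times too small. Under a −20% per year trend the mean RR was 0.79, with empirical SD 0.083 against robust SE 0.079. That is bias with a nearly correct SE. A 30% city-wide drop at mid roll-out gave RR 0.70; a late 30% rise gave RR 1.13.

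**5. With month effects.** Using Mancl-DeRouen standard errors and a t reference on 14 degrees of freedom, false positives were 2.5% to 4.5% in every scenario. With uncorrected standard errors they were 8% to 13% (6% to 9% in the second set). The same correction with the harmonic alone left 27%, 51% and 59% for the three shock SDs, so correcting for few clusters does not replace adjusting for time.

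**The case against.** The strongest reply is that the article is condensed, does not call its covariate list complete, and offers other safeguards. A treatment-by-time interaction would normally bring a time main effect. Deviations from the calendar are to be documented and accounted for, confounders may be added, and the service indicator varies over time. Some of this stands: a fuller analysis plan could add period effects, and the simulations did not include a service indicator. But the interaction is only to be considered, the confounders listed are patient and location factors, a service indicator does not track outbreaks or vaccination, and the ITS has no concurrent control.

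Four stronger readings might be inferred, and the documents do not support them:

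- **Every city-wide event becomes intervention effect.** Only the part aligned with roll-out and missed by the harmonic does. The late 30% rise leaked in only partly.
- **Shocks during roll-out are certain.** The flood is dated April 2020. A July 2022 end and a roll-out of under two years imply a start after the flood, and the trial diagram is not shown. Overlap cannot be established.
- **The article forecasts a fall that produces a false reduction above 25%.** That needs the Table 1 baseline, and the figure belongs to a sensitivity analysis. In the trial period even that slope gives 0.91 to 0.96.
- **Adding period effects costs no power.** The article names only the sample-size command, and the interval does widen.

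**Conclusion.** The point holds. As written, the primary analysis of both outcomes lacks the time adjustment that lets randomised step order protect against secular change, and no listed sensitivity analysis restores it.

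The direction of the problem follows from the design; its size rests on assumptions. With city-wide shock SDs of 0.2 to 0.6, robust standard errors are roughly 2 to 4 times too small and false-positive rates about 25% to 65%. With a smooth trend the fault is bias: a trial-period null RR of 0.91 to 0.96 at −5% per year, and close to 1 at −1.3%. The historical re-fit is more exposed, with a null RR of about 0.71 to 0.75 or about 0.92 to 0.93 according to the baseline. The article's rates do not settle which applies.

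**What to change.** In the primary GEE, for suspected and confirmed cases, add a fixed effect for each calendar month or step, or a flexible spline of calendar time if monthly effects are too many for 16 clusters. Commit to a small-sample correction, for example Mancl-DeRouen standard errors with a t reference. Add year or flexible calendar-time terms to the historical re-fit. Keep the harmonic-only model as a sensitivity analysis at most.

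Two costs should be stated:

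- **Precision.** Under the assumed overdispersion and no shocks, the SD of the log RR rises from about 0.09 to 0.14. The detectable reduction becomes 1 − exp(−2.80 × 0.142) = 33%, so the 25% figure needs to be rechecked and restated for this model. Month effects also left a null mean RR of 0.93 to 0.97 in the simulations, an artefact of few, unequal clusters.
- **Estimand.** Period effects absorb improvements that reach all clusters at once, such as the treatment plant and the new tank. The stepped-wedge estimate then refers to the randomised cluster-level works, and the city-wide components are left to the ITS. The article should say so.

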**Fig. 1 Fig1:**
[figure not shown]
Map of Uvira with the definition of clusters and groups: South (blue, *n* = 6) and North (pink, *n* = 10)

**Table 1 Tab1:** Key cluster characteristics

Cluster #	Estimated population (March 2018)	Area [km^2^]	*Mean # suspected cholera cases per month	*Mean monthly incidence per 1000	Existing pipe length [m]	Pipe length to rehabilitate [m]	Length of new pipes to install [m]	# existing household connections	# provisionally planned new household connections	Number of planned new community taps	Allocation sequence
1	4291	2.02	1.9	0.4	2152	57	2628	16	66	6	15
2	4990	0.76	6.0	1.2	1578	1658	1792	89	25	3	16
3	11,183	0.87	6.4	0.6	5574	1266	1864	171	25	7	10
4	7328	1.02	5.4	0.7	2347	0	3398	25	100	5	12
5	13,649	1.27	4.4	0.3	2786	797	4177	19	205	4	9
6	8389	0.48	5.8	0.7	1730	499	2328	43	82	6	13
7	7480	0.37	2.0	0.3	4525	367	1065	152	26	2	8
8	15,455	0.43	4.8	0.3	2961	1097	1793	199	25	5	7
9	3994	0.36	9.4	2.4	3848	189	2446	183	25	8	11
10	14,175	0.59	7.1	0.5	8901	692	1520	525	25	7	1
11	56,106	1.70	14.5	0.3	8775	1599	2401	633	254	16	5
12	12,462	0.99	3.0	0.2	2292	1455	1844	22	193	1	14
13	50,764	2.75	10.4	0.2	17,781	1666	1266	1384	24	11	4
14	16,175	0.55	6.7	0.4	907	0	2549	35	220	5	3
15	15,183	0.81	7.2	0.4	4091	135	2420	161	62	9	2
16	19,338	1.98	10.6	0.6	1788	2061	2874	28	318	20	6
**Mean**	**16,310**	1.06	6.6	0.4**	72,033	13,538	36,363	3685	1675	7.2	–
Minimum	3994	0.36	1.9	0.2	907	0	1065	16	25	1	–
Maximum	56,106	2.75	14.5	2.4	17,781	2061	4177	1384	318	20	–

*Based on CTC admissions between January 1, 2009, and March 31, 2018, and population in March 2018

**Mean weighted by cluster population size

Within each group (South and North), clusters were randomised to different initiation periods by the research team using a random number generator, with the intervention delivered to the South clusters first. The intervention interval—or “step”—during which time a given cluster receives the intervention was planned to be 4 weeks; this interval was extended to up to 8 weeks for the installation of new household connections to the water supply network (Fig. 2)—the reasons are discussed below.

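### The plan commits both primary tests to robust standard errors on 16 clusters but leaves the small-sample correction optional; without it the nominal 5% test runs at roughly 8 to 15%

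*Protocol article*

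**What the plan says.** The Analysis plan of the Protocol article states the primary method firmly: "A generalised estimating equations (GEE) Poisson regression for rates will be used with robust standard errors". Time is handled by a seasonal term: "To account for seasonality a harmonic term for time (in months) will be included". Transition data are dropped: "data collected during the transition period for each cluster will not contribute to the analysis". The same models are then repeated for the other primary outcome, so one inferential choice serves both suspected and confirmed cholera.

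On few clusters the wording is weaker: "A small sample correction will be considered to adjust for the small number of clusters". A reference is cited, but the text does not say whether a correction will be used, which one, or with what reference distribution.

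Under Description and diagram of trial design, "The town of Uvira was divided into sixteen clusters stratified into two groups": South with 6 clusters and North with 10. The order was drawn at random separately in the two groups: "clusters were randomised to different initiation periods by the research team using a random number generator". All South clusters are scheduled ahead of the North ones. The Sample size section takes the error rate at face value: "Power was set at 80% with a 5% significance level".

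**The concern.** The robust (sandwich) variance is justified when the number of clusters is large. With 16 clusters it tends to be too small, and referring the Wald statistic to the normal distribution adds to the problem. Both push the same way: intervals too narrow and too many false positives. The plan makes the vulnerable part firm and the remedy optional.

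Both primary tests are at stake. The candidate corrections do not give the same answer, so an open choice among none, a t reference alone, and a bias-corrected standard error can move a p-value across 0.05. The Introduction of the article says that the protocol and analysis plan are published for the sake of pre-specification, and a remedy left open works against that aim.

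**Working it through.** **1. The plan's own figure.** Inputs from Sample size: rate 0.4 per 1000 per month, ICC 0.3, mean cluster size 16,000, two-sided 5%, power 80%. Assumed: 16 clusters crossing one per step, with one baseline period, so T = 17. The Hussey-Hughes variance is

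Var = Iσ²(σ² + Tτ²) / [(IU − W)σ² + (U² + ITU − TW − IV)τ²]

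with I = 16, U = 136, W = V = 1496, p = 0.0004, σ² = p(1 − p)/16,000 = 2.50 × 10⁻⁸ and τ² = (0.3/0.7) × p(1 − p). Here τ² dominates, so Var ≈ 16 × 17 × 2.50 × 10⁻⁸ / 6120 = 1.11 × 10⁻⁹ and SE = 3.33 × 10⁻⁵. The detectable difference is (1.960 + 0.842) × SE = 0.093 per 1000. Reading the ICC as a share of the total variance gives 0.078. Both round to the stated 0.1, so the design figure reproduces. It assumes that the test really has size 5%.

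**2. The clusters.** From Table 1, the population total is 260,962, the mean 16,310 and the coefficient of variation 0.93. Clusters 11 and 13 hold 106,870 / 260,962 = 41% of the population, but 24.9 / 105.6 = 24% of monthly cases. The effective number of clusters, (Σx)²/Σx², is 8.8 by population and 12.9 by cases.

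**3. Size of the test under no effect.** Data were Poisson with seasonality and Table 1 populations (equal sizes as a variant), with South first. The order was re-randomised within group or taken as published. The model was GEE Poisson with the harmonic term (period effects as a variant). There were 800 to 1500 runs per setting, with Monte Carlo standard error about 0.7 to 1.4 points. Assumed, because the document does not give them: between-cluster SD of the log rate 0.3 to 0.6 (Table 1 gives about 0.63) or Table 1 rates held fixed; cluster-period SD 0 to 0.4; autocorrelation 0 to 0.7; a binary intervention indicator; 1 or 2 transition periods; 1 or 12 periods before and after. The t reference has 16 − 2 = 14 degrees of freedom.

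Selected rejection rates (%) at nominal 5%. SDs are given as cluster / cluster-period, then autocorrelation; the working correlation is exchangeable unless stated.

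| Setting | Uncorrected, z | Uncorrected, t(14) | Kauermann-Carroll, t(14) | Mancl-DeRouen, t(14) |
|---|---|---|---|---|
| Harmonic, Table 1 rates fixed, published order | 8.7 | 6.9 | 5.6 | 4.5 |
| Harmonic, Table 1 rates fixed, re-randomised | 9.9 | 7.5 | 6.2 | 4.7 |
| Harmonic, 0.3 / 0.2, 0 | 10.8 | 7.9 | 6.4 | 4.9 |
| Harmonic, 0.3 / 0.2, 0, equal sizes | 8.7 | 6.5 | 5.5 | 4.7 |
| Harmonic, 0.6 / 0.4, 0.7 | 14.8 | 12.7 | 9.9 | 8.2 |
| Harmonic, 0.6 / 0.4, 0.5, independence, 12 periods before and after | 15.5 | 11.4 | 8.5 | 5.9 |
| Period effects, Table 1 rates fixed, published order | 6.7 | 4.9 | 3.6 | 2.2 |
| Period effects, 0.6 / 0.4, 0.7 | 18.8 | 14.9 | 11.4 | 7.8 |

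A second simulation with Table 1 populations and a harmonic model gave 7.5 to 14% uncorrected, and about 3 to 7% for Mancl-DeRouen with t(14).

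Two runs are left out of the ranges: independence working correlation with Table 1 rates fixed rejected 20% (harmonic) and 29% (period effects). There the estimate itself is biased because South goes first, which is a different problem from the standard error.

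**4. Reading.** The uncorrected z test exceeded 5% in every setting. A t reference alone leaves about 5 to 13% in all but the least favourable period-effects runs. Mancl-DeRouen with t(14) is closest to nominal, though not exact.

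**The case against.** The strongest reply is that the document never says the test will be uncorrected. It names the problem, points to a correction and cites a source. Which correction and which degrees of freedom are matters that an article may leave to a statistical analysis plan that is not shown. This stands in part. A reader might infer that the primary test is uncorrected and rejects a true null at some fixed rate near 10%. The text supports neither: the inflation is conditional on no correction being used, and its size depends on variance components that the document does not give. Nor does any section say that the choice will be made after seeing the data. What remains is not a missing detail but a sentence about primary inference that, as worded, allows either outcome.

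A reader might also infer that two very large clusters are the main cause, leaving about nine effective clusters. That is a population-based count. By cases, which carry more of the information in a rate model, it is about 13, and equal cluster sizes still gave roughly 9 to 14%. Inequality contributes, but the small number of clusters is enough by itself.

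A third tempting step is to make a permutation test within South and North the primary method, because that matches the randomisation. The Analysis plan and the Discussion both foresee that the sequence may not be followed. The exposure may also enter through an indicator of water service quality, to which re-randomising the order does not carry over directly. The same indicator is a caveat on the simulations, which used a binary exposure.

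**Conclusion.** The concern holds in conditional form. If no correction is applied, the nominal 5% test of either primary outcome has a true size of roughly 8 to 15% under the planned harmonic model, so a nominal 95% interval would cover about 85 to 92%. Over wider assumptions the size is about 7 to 19%. The direction is robust; the exact figure is not, for the reasons listed with the inputs. The stated detectable difference is not wrong at its printed precision. This is a cheap improvement to the wording of the primary analysis, not an error that undermines the design.

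**What to change.** Replace the sentence that leaves the correction open with a commitment, made before outcome analysis and applying to both primary outcomes: a named bias-corrected sandwich (for example Mancl-DeRouen or Fay-Graubard) with a t reference on clusters minus cluster-level parameters. Report the uncorrected result only as supplementary. A permutation test within South and North can be added as a sensitivity analysis if the randomised sequence is followed.

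The cost is wording, a little computing and somewhat wider intervals. The t(14) multiplier alone widens them by 2.145 / 1.960 = 1.09. In the design formula it raises the detectable difference by (2.145 + 0.868) / (1.960 + 0.842) = 1.075, from 0.093 to 0.100 per 1000. The corrected standard error adds to this by an amount the document does not allow one to compute.

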## World Health Organization Trial Registration Data Set

**Table Taba:** 

#	Item	Description
1	Primary Registry and Trial Identifying Number	*clinicaltrials.gov*, NCT02928341
2	Date of Registration in Primary Registry	10th October 2016
3	Secondary Identifying Numbers	LSHTM Ethics Review Board protocols #8913, #10603
4	Source(s) of Monetary or Material Support	French Agency for Development (AFD) Veolia Foundation (VF)
5	Primary Sponsor	London School of Hygiene and Tropical Medicine (LSHTM)
6	Secondary Sponsor(s)	None
7	Contact for Public Queries	[name], Principal Investigator, [contact] [name] [name]
8	Contact for Scientific Queries	
9	Public Title	Impact Evaluation of Urban Water Supply Improvements on Cholera and Other Diarrhoeal Diseases in Uvira, Democratic Republic of Congo
10	Scientific Title	The impact of improved water supply on cholera and diarrhoeal diseases in Uvira, Democratic Republic of the Congo: a pragmatic stepped-wedge cluster randomised trial and economic evaluation
11	Country of Recruitment	Democratic Republic of the Congo
12	Health Condition(s) or Problem(s) Studied	Cholera, diarrhoeal disease
13	Intervention	Control: current water supply service Intervention: improved water supply service (new and rehabilitated supply network infrastructure including community and household tap connections)
14	Key Inclusion and Exclusion Criteria	Inclusion Criteria: Uvira resident (without restriction placed on age or sex) admitted to the Uvira Cholera Treatment Centre at the General Hospital in Uvira Exclusion Criteria: Any patients admitted during the period of intervention implementation in each cluster
15	Study Type	Interventional; stepped-wedge cluster randomised trial
16	Date of First Enrolment	10th October 2016
17	Sample Size	Planned enrolment: 5000 Enrolment to date: 4280
18	Recruitment Status	Recruiting
19	Primary Outcome(s)	(1) monthly incidence of suspected cholera cases, as measured by the number of CTC admissions attributed to each cluster; (2) monthly incidence of confirmed cholera cases, based on rapid detection test (RDT) results for consenting patients
20	Key Secondary Outcomes	None
21	Ethics Review	Approved. LSHTM Ethics Committee: #8913, 14th December 2015; #10603, 7th April 2016 Kinshasa School of Public Health Ethics Committee: ESP/CE/088/2015, 4th September 2015 (last renewal: ESP/CE/143/2020, 23rd August 2020)
22	Completion Date	Expected 27th September 2021

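### The seasonality re-fit counts all CTC data since 2009 as control time with no year or era term, so a secular fall of the size the protocol projects would appear as a 20-30% intervention effect on suspected cases

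*Protocol article*

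**What the plan says.** The Analysis plan specifies a Poisson GEE for rates with robust standard errors. Two covariates are named. One is seasonal: "To account for seasonality a harmonic term for time (in months) will be included". The other describes the service: "An indicator of water service quality will be included, which may integrate users’ distance to taps, hours of water availability, or volumes distributed".

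Because the roll-out lasts under two years, the plan doubts that trial data alone can estimate the seasonal pattern. It therefore adds "historical data from the cholera treatment centre which is available from 2009 to the start of the trial" in a sensitivity analysis, with this rule: "The model will be re-fitted using the same covariates, with all historical data considered non-intervention time". A further option follows: "We will also consider the inclusion of a treatment by time interaction term in the GEE model". The same models are to be repeated for confirmed cases.

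The Sample size section uses a pre-intervention rate of 0.4 per 1000 per month for the stepped wedge. For the interrupted time series it models the historical CTC data with a linear year term and harmonic month terms, and reports: "The mean monthly rate per 1000 people was estimated to be 0.25 over a 12 month follow-up, 0.29 over 6 months". Those follow-up periods start from July 2022.

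**The concern.** The registered comparator is "Control: current water supply service", and a stepped wedge compares treated clusters with clusters still waiting at the same time. The re-fit needs the old data only to estimate the harmonic. By coding every month since 2009 as non-intervention with no term that separates old from new, it also lets those months serve as controls. About eleven years of non-concurrent control time then outweigh less than two years of trial time.

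That is harmless only if the underlying rate is stable. The protocol's own projection says it is not: it falls from 0.40 to about 0.25 with no intervention effect in the model. The year term used to size one analysis is missing from another that uses the same series. At stake is the stated check on whether poorly estimated seasonality distorts the main result. It could show a reduction close to the 25% the trial is sized to detect even if the works did nothing.

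**Working it through.** **Inputs.** Populations, mean monthly suspected cases and allocation sequence come from Table 1. The projected rates 0.25 and 0.29 come from the Sample size section. The under-two-year roll-out and the dropped transition period come from the Analysis plan and the trial design text. Assumed: roll-out from mid-2020, 19 four-week periods, two periods dropped per cluster, a log-linear trend, and no intervention effect. The water-service indicator is not modelled, because its definition is open.

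**Reproducing the baseline.** Table 1 sums to 105.6 cases per month in 260,962 people. 105.6 / 260,962 = 0.405 per 1000 per month, which matches the stated 0.4. 105.6 × 12 = 1267 per year, against the stated 1266.

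**Trend.** The midpoint of January 2009 to March 2018 is 2013.62. The midpoint of the 12 months after July 2022 is 9.46 years later.
- To 0.25: k = ln(0.25/0.405)/9.46 = -0.051 per year.
- To 0.29: k = ln(0.29/0.405)/9.46 = -0.035 per year.

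**Rough check by hand, trend to 0.25.** The rate at time t is 0.405 × exp(k(t - 2013.62)).
- Historical control time, midpoint about 2014.75: 0.405 × exp(-0.051 × 1.13) = 0.38.
- Trial period, midpoint about 2021.2: 0.405 × exp(-0.051 × 7.6) = 0.27.
- Ratio 0.27/0.38 = 0.71. For the trend to 0.29 the same steps give 0.31/0.39 = 0.79.

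**Model fits on expected counts (true rate ratio 1.00), suspected cases, with cluster effects.**

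| Fit | Trend to 0.25 | Trend to 0.29 |
|---|---|---|
| Historical re-fit, no year or era term | 0.71 | 0.79 |
| Trial-period data only | 0.96 | 0.97 |
| Re-fit with historical-versus-trial indicator | 0.97 | 0.98 |
| Re-fit with linear year term | 1.00 | 1.00 |

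A weaker trend, to 0.33, gives 0.87 for the re-fit without a year or era term. An exchangeable GEE on the Table 1 cluster rates, with the trend to 0.25, gives a 26-30% reduction, so the cluster-effects figures are a fair guide to the planned model.

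**Separating cluster mix from old data.** With an independence working correlation and no cluster terms, the re-fit gives 0.63 for the trend to 0.25. The same fit with no trend at all already gives 0.89, because some small, high-rate clusters (2 and 9, for example) come late in the sequence. Only the figures with cluster effects isolate what pooling the old data does.

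**Confirmed cases.** Swab collection was offered from April 2016 (Recruitment and consent), so there is no confirmed series back to 2009. Applying the same trend from April 2016 gives a spurious reduction of about 10-14% with cluster effects.

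**The case against.** The strongest reply is that the fall is not established. The protocol gives no yearly rates, trend coefficient or interval. It gives one average on a fixed March 2018 population and one extrapolation whose denominator is not stated, so part of the drop could be a change of denominator. The 0.29 is a six-month mean and partly seasonal, so it is not a second trend endpoint; it serves here only as a milder scenario. The Study setting section also gives 3.4 admissions per 1000 per year. That is 3.4/12 = 0.28 per month, and starting from it the bias would be only 7-9%. All this stands as a limit on size. The 3.4 does not sit well with the protocol's other figures, however: 1266/280,000 is 4.5 per 1000 per year, or 0.38 per month.

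It can also be said that the re-fit inherits its covariates from the main model, so a calendar-time term added there would carry over. That is true, and it would be a valid route to the same repair. But the missing trend costs only 3-4% on trial-period data with cluster effects; pooling the old data raises it to 20-30%. The treatment-by-time interaction does not settle the matter. It is only to be considered, and it is not stated to include a main effect of calendar time.

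A reader might infer more than the documents support:
- A bias of 37%. That is about the raw ratio of 0.25 to 0.40, or a fit without cluster terms that is partly cluster mix.
- Very small standard errors. None is reported, and robust errors are planned with a small-sample correction under consideration.
- A model with a harmonic only. The water-service indicator is also named, and its effect on the bias cannot be worked out from the article.
- That the result would be taken as confirming the main finding. This is possible but is conjecture.

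**Conclusion.** The point holds as a defect in one stated sensitivity analysis. If the secular fall implied by the protocol's own projection is real, the re-fit attributes it to the intervention. For suspected cases the spurious reduction is roughly 20-30% (about 13% under the weaker trend to 0.33), and for confirmed cases about 10-14%. The direction follows from any downward trend. The size rests on the log-linear shape, the assumed start date, comparable denominators behind 0.40 and 0.25, and leaving the water-service indicator out.

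The primary analysis does not depend on this re-fit, and the separate interrupted time series is unaffected. The change should be made before the data are analysed, but it does not threaten the trial's main result.

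**What to change.** Replace the rule that all historical data count as non-intervention time with one of two specifications:

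1. Re-fit on historical plus trial data with the linear year term already used in the Sample size section, together with cluster effects. The null rate ratio is 1.00 if the trend is log-linear.
2. Re-fit with a historical-versus-trial indicator and cluster effects. The null rate ratio is 0.97-0.98. This does not depend on the shape of the trend before the trial, but leaves the small drift within the trial period.

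Cluster effects are needed in either case. In the calculations with unequal cluster rates, a year term without them still left a spurious reduction of about 7-15% from cluster mix. For confirmed cases, state that the historical series starts in April 2016.

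Either way, the old data inform the seasonal terms and the intervention effect no longer rests on an old-versus-new contrast. The cost is a sentence in the plan, a few extra model terms and a somewhat larger standard error in this one analysis. No new data are needed.
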